## Abstract

**Background:**

The treatment of large (10-25 mm) or giant (≥25 mm) cerebral aneurysms remains technically challenging, with a much higher complication and recanalization rate than that is observed for smaller aneurysms. The use of a flow diverter seems to facilitate the treatment of this special entity. In a previous single-center prospective study approved by the Ethics Committee and China Food and Drug Administration (CFDA), we obtained promising results, showing remarkable safety and effectiveness for the Tubridge flow diverter. Nevertheless, the previous study may have been limited by biases due to its single-center design and limited number of subjects. Furthermore, although various articles have reported durable results from treating aneurysms using flow diverters, increasing questions have arisen about this form of treatment. Thus, prospective, multiple-center, randomized trials containing more subjects are needed.

**Methods/Design:**

This study is a multicenter, randomized, controlled clinical trial comparing clinical outcomes for patients with unruptured large/giant intracranial aneurysms treated with either conventional stent-assisted coiling or flow diverter implantation. A total of 124 patients who fulfill the inclusion and exclusion criteria will be randomized into either a treatment group or a control group in the ratio of 1:1. The treatment group will receive Tubridge implantation alone or combined with bared coils, and the control group will be treated with stent-assisted coiling (bare coils). The primary endpoint will be the complete occlusion rate at 6-month follow-up. Secondary endpoints include the immediate technique success rate, overall mortality, adverse events (ischemic stroke or intracranial bleeding) within 30 days, 90 days and 1 year post-operation, and the rate of intra-stent stenosis and thrombosis 6 months post-operation.

**Discussion:**

This prospective trial may provide more information on the safety and efficacy of the Tubridge flow diverter and may potentially change the strategy for treatment of large or giant aneurysms.

**Trial registration:**

The trial is registered on the Chinese Clinical Trial Registry: ChiCTR-TRC-13003127

## Background

Intracranial aneurysms are pathological bulges of cerebral arteries caused by various etiologies, such as inflammation or hemodynamic stress. Their rupture often results in a catastrophic outcome, and they are associated with high rates of mortality and morbidity [1]. Large (10-25 mm) or giant (≥25 mm) aneurysms are a subtype of intracranial aneurysm with a much higher rupture risk and poorer outcomes compared with small aneurysms [2,3]. Despite technical advances, the treatment of large or giant aneurysms remains technically challenging, with a much higher complication and/or recanalization rate [4-8].

In recent years, with better understanding of the occurrence and development of intracranial aneurysms, the concept of vessel reconstruction, especially flow diversion, has attracted the interest of neurointerventionalists worldwide. Accordingly, various flow diversion devices have emerged around the world; the best known devices include the Pipeline (ev3, Irvine, CA, USA) and the Silk (Balt Extrusion, Montmorency, France), which gained the approval of the FDA and the CE and have been used clinically in over 50 countries [9-16].

Compared with conventional endovascular treatment such as stent-assisted coiling, the Flow Diverter (FD) can alter the blood flow, reduce the hemodynamic stress in the aneurysm neck, and promote intra-saccular thrombus formation [17-20]. A series of studies have shown that flow diverters can significantly improve the outcome of intracranial aneurysms [9-11,13,14,16].

The Tubridge is a new type of flow diversion device developed by MicroPort Medical Company (Shanghai, China) based on our previous clinical experience of multiple stenting in intracranial aneurysms and the hemodynamic study of intracranial aneurysms. Referring to its structure, the Tubridge FD is actually a braided, self-expanding “stent-like” device with flared ends. Currently, Tubridge FDs are available in many diameters (2.5-6.5 mm) and lengths (12–45 mm). A large Tubridge (diameter ≥3.5 mm) is braided with 62 nickel- titanium microfilaments and 2 platinum-iridium radiopaque microfilaments, whereas a smaller Tubridge (diameter <3.5 mm) is composed of 46 nitinol and 2 platinum-iridium microfilaments. All Tubridge FDs were designed with a pore size of 0.040-0.050 mm^2^ at a nominal diameter, aiming to provide a high metal coverage (approximately 30.0%-35.0%) at the aneurysmal neck after full opening. In addition to its use of a nickel-titanium alloy (commonly known as nitinol, which has the advantages of shape-holding memory and super-elasticity) and flared ends, the Tubridge FD offers some structural improvements compared with the Pipeline and the Silk. The use of platinum-iridium material for the radiopaque microfilaments allows for improved visualization of both diameter and length during the procedure. More importantly, the design, which includes more braided microfilaments for large-size FDs, decreases the shortening rate of the FD after its full opening.

In a previous single-center prospective study approved by the Ethics Committee and China Food and Drug Administration (CFDA), we obtained promising results, showing remarkable safety and effectiveness for the Tubridge FD. In that study(data in press), a total of 33 Tubridge FDs were successfully implanted for 28 large or giant aneurysms, with the exception of one mid-stent with a poor opening, resulting in a technical success rate of 97.0% (32/33). Follow-up angiographies, taken at a mean follow-up of 9.9 m (5–24 m), were available for 25 aneurysms. Of those, 18 (72.0%) aneurysms were completely occluded, 6 (24.0%) were improved, and 1 (4.0%) was unchanged. All visible covered branches and the parent artery were patent, with no stenosis or obliteration. During a follow-up period of 6 to 30 months (mean 19.0 months), the symptoms experienced were resolved in 13 patients, improved in 6, and showed no change in 4. No procedure-related morbidity or mortality occurred. Nevertheless, biases may exist in the study due to its single-center design and limited number of subjects. Prospective, multiple-center, randomized trials that include more subjects are needed.

Furthermore, although various articles have reported durable results from treating aneurysms with FDs, increasing questions have arisen about this type of treatment. For example, is the occurrence of peri-procedure intra-parenchymal hemorrhage accidental or related to the application of the device? Are ischemic complications encountered more often with FDs than with conventional therapy [21-25]? These questions need to be answered through prospective trials, which have been lacking to date.

Based on these considerations, we initiated this trial with the aim of evaluating the safety and effectiveness of the Tubridge FD for unruptured large or giant aneurysms (≥10 mm).

## Methods

### Objectives

The aim of the trial is to assess the safety and effectiveness of the Tubridge flow diverter in the treatment of unruptured large or giant intracranial saccular aneurysms.

### Study design

This study is a multicenter, randomized, controlled clinical trial comparing clinical outcomes for patients with unruptured large/giant intracranial aneurysms treated with either conventional stent-assisted coiling or with flow diverter implantation. The study will be conducted in 13 centers, each of which have performed more than 30 stent-assisted coiling procedures per year in the past 5 years, after gaining approval from local ethics committees. A total of 124 patients who fulfill the inclusion and exclusion criteria will be randomized into either a treatment group or a control group in the ratio of 1:1. The treatment group will receive Tubridge FD implantation alone or combined with bare coils, and the control group will receive stent-assisted coiling (bare coils). Procedure-related complications, adverse events, and follow-up data will be collected prospectively to evaluate the safety and effectiveness of the Tubridge FDs.

### Hypothesis

Compared with conventional stent-assisted coiling, Tubridge FD implantation does not enhance the risk of procedure-related complications and may lead to a higher complete occlusion rate and a decreased recanalization rate.

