### Planned analyses

Statistical analyses will be conducted based on an intention-to-treat (ITT) population. Participants who are recruited and treated will be considered the full analysis set (FAS), those who complete treatment and the entire follow-up protocol will be considered the per-protocol set (PPS), and those who are treated and have at least one safety evaluation will be considered the safety set (SS). Last observation carried forward (LOCF) method will be implemented to handle the missing data from withdrawn subjects, who would be included in FAS.

Comparisons of demographic information will first be conducted to measure the balance between the two groups. Then evaluation of primary and secondary outcome will conducted as below:

Primary outcomes:

The comparison of the treatment groups with regard to the primary endpoint will be performed with the data of the Full Analysis Set as well as of the Per Protocol Set. In case the two analyses will lead to different conclusions the result of the analysis of the Per Protocol Set is deciding.

Use superiority test for analysis of primary outcome. The formal test problem is as follows:

Test problem for the complete occlusion rate at 6-month follow-up:

Let πT be the rate of complete occlusion rate of treatment group at 6-month follow-up.

Let πc be the rate of complete occlusion rate of control group at 6-month follow-up.

The superiority margin δ is 0.

Test problem:

H0: πT -πc ≥ 0

H1: πT -πc < 0

α = 0.05 (2-sided)

The alternative hypothesis will not be accepted unless the lower limit of the 95% confidence interval of the difference of occlusion rate lies above the superiority margin.

Secondary outcomes:

Immediate occlusion rate will be conducted in FAS group, while other safety evaluation will be be conducted in SS group. For quantitative data, t-test (for equal variances and normal distribution) or Wilcoxon rank sum test could be applied according to the distribution of the data. The categorical variables will be compared between study arms using Chi-square tests or Fisher's exact tests (if Chi-square test is not valid). Besides, for immediate technique success rate, 95% confidence interval of each groups and difference between groups will be estimated.

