## Discussion

Large and giant aneurysms carry the risk of a significantly worse outcome compared with small aneurysms [3]. The ISUIA study showed that the risks of rupture within 6 years for large and giant aneurysms are as high as 13% and 27%, respectively [2]. The treatment of this entity, whether with conventional endovascular treatment or surgery, imposes a great challenge for both neurosurgeons and neurointerventionalists. A deconstructive approach such as internal carotid artery(ICA) occlusion requires sufficient compensation from other vessels; even so, rates of ischemia as high as 4%-15% have been recorded [7]. In addition, there are also concerns about de novo aneurysm following ICA occlusion [31]. Bypass surgery, especially high-flow bypass, preceding ICA occlusion may help reduce ischemic complications, but operative complications are not uncommon, though reports in different manuscripts vary [32]. In contrast, reconstructive approaches such as stent-assisted coiling aiming to preserve the parent artery are associated with much higher recanalization rates, ranging from 19.2% to 50%. However, the use of FDs, including Pipeline, Silk, and Tubridge, have recently shown excellent and promising results [9-14,16]. Because of this, we began this prospective trial, which may provide more information on the safety and efficacy of the Tubridge flow diverter and may change the treatment strategy for large or giant aneurysms if the hypotheses are confirmed.

A similar trial, MARCO POLO, which was designed to compare the results of coiling (with balloon remodeling and/or stents when necessary) to those of Silk FD implantation, is being conducted in 7 countries around the world [33]. However, there are apparent differences between our trial and MARCO POLO, such as the target aneurysms and the different active comparators used.

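### The hypothesis that the flow diverter does not raise complication risk has only difference tests behind it, and a non-significant difference test cannot support it

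*Protocol article*

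**What the plan says.** The Hypothesis section states, as the safety half of the trial hypothesis, that "Tubridge FD implantation does not enhance the risk of procedure-related complications". The gains in occlusion and recanalization are worded as possibilities; the safety clause is not. The Background names harm among the open questions the trial should help answer: "Are ischemic complications encountered more often with FDs than with conventional therapy". The Discussion says the trial "may change the treatment strategy for large or giant aneurysms if the hypotheses are confirmed".

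Planned analyses gives a formal test problem, with a confidence-interval decision rule, for complete occlusion at 6 months only. The one margin in the article belongs to that endpoint: "The superiority margin δ is 0". On safety it says that "other safety evaluation will be be conducted in SS group" and gives this method: "The categorical variables will be compared between study arms using Chi-square tests or Fisher's exact tests (if Chi-square test is not valid"). It then adds that "for immediate technique success rate, 95% confidence interval of each groups and difference between groups will be estimated". No other secondary outcome is given an interval for the difference. The article gives neither an expected complication rate for coiling nor an excess risk to be excluded. Sample size rests on occlusion alone.

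**The concern.** A claim that risk is not increased is a claim about the largest excess compatible with the data. Chi-square and Fisher tests take equality as the null hypothesis. They can give evidence of a difference, but failing to reject is not evidence that there is none. So the method the article fixes does not answer the hypothesis the article states, and nothing else in the article does.

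This mismatch exists at any sample size. A small trial makes it matter more, because non-significance is then a likely result even when the risk has truly doubled. What is at stake is the conclusion on stroke and bleeding, a question the Background says prospective trials must answer.

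**Working it through.** **1. The plan's own figure.** Inputs from Sample size: 35% v 65% complete occlusion, two-sided α = 0.05, power 0.80, 20% withdrawal.
- Without continuity correction: n = [1.96·√(2·0.5·0.5) + 0.8416·√(2·0.35·0.65)]² / 0.30² = (1.386 + 0.568)² / 0.09 = 42.4, so 43 per arm.
- With continuity correction: (42.4/4)·[1 + √(1 + 4/(42.4·0.30))]² = 48.9, so 49 per arm.
- Withdrawal: 49/0.80 = 61.25, so 62 per arm and 124 in total.

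The stated 49 and 62 reproduce. They use efficacy inputs only.

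**2. Power of the planned safety tests for a doubling of risk.** Inputs: 62 per arm (Sample size), two-sided 0.05. Event rates are assumed because the article gives none for the control arm. The article uses Fisher when Chi-square is not valid; I assume this means an expected count below 5. With a events in the flow-diverter arm and b in the control arm,

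power = Σ over a > b of Bin(a; 62, p_T)·Bin(b; 62, p_C)·1{test significant}.

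The uncorrected Chi-square test is significant when |a − b|/62 > 1.96·√(2·p̄(1 − p̄)/62), with p̄ = (a + b)/124. Fisher is significant when its two-sided p ≤ 0.05. The smallest expected count is (a + b)/2, so the combined rule uses Fisher when a + b < 10.

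| Control v flow diverter (assumed) | Chi-square always | Fisher always | Planned rule |
|---|---|---|---|
| 3% v 6% | 11% | 4% | 4% |
| 5% v 10% | 18% | 9% | 15% |
| 10% v 20% | 34% | 26% | 34% |
| 15% v 30% | 52% | 44% | 52% |
| 20% v 40% | 69% | 62% | 69% |
| 25% v 50% | 83% | 78% | 83% |

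At 10% v 20% the rule calls for Fisher in under 1% of trials, so 34% is the relevant figure there, not 26%. If only 49 per arm were evaluable, the planned rule would give about 2%, 9%, 29%, 43%, 58% and 73% down the rows.

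**3. What an interval would show.** Suppose 6/62 events with the flow diverter and 3/62 with coiling (illustrative counts close to 10% and 5%). Here a + b = 9 < 10, so Fisher applies: p = 0.49. The 95% Wilson limits are 4.5% to 19.5% for 6/62 and 1.7% to 13.3% for 3/62. Newcombe's interval for the difference of 4.8 points is
- lower: 4.8 − √[(9.7 − 4.5)² + (13.3 − 4.8)²] ≈ −5.1 points;
- upper: 4.8 + √[(19.5 − 9.7)² + (4.8 − 1.7)²] ≈ +15.2 points.

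The test reports no significant difference, while the interval shows that an excess of about 15 points is not excluded.

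**4. What a formal no-excess claim would need.** With equal true rates p in both arms, one-sided 0.025 and 80% power, n = (1.96 + 0.8416)²·2p(1 − p)/margin². Margins are assumed.
- 10-point margin: 75, 142 or 201 per arm at p = 5%, 10% or 15%.
- 5-point margin: 299, 566 or 801 per arm.

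A margin-based claim is therefore not a cheap addition at 62 per arm: power for a 10-point margin is 72%, 46% or 34% at those rates.

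**The case against.** A reader might infer that the trial will declare safety confirmed whenever p>0.05. The documents do not say so. Planned analyses sets a decision rule for the primary endpoint only and says merely that safety variables will be compared. The Discussion sentence is hedged, and the hypotheses it refers to include occlusion and recanalization. That reading is a risk the text leaves open, not a stated rule.

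A reader might also infer that the trial is too small. Safety is secondary, the sample size is right for the occlusion inputs, and the article never claims safety power. Low power on secondary safety outcomes is no defect in itself; here it only shows how little a non-significant result would mean.

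It would be wrong, too, to say that intervals are planned only for technique success. The primary endpoint is judged by the 95% interval for the difference, and the sentence on technique success does not rule out intervals elsewhere. An unseen analysis plan may add them.

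Finally, all event rates are assumed. For common events, such as general adverse events, a doubling could be detected reasonably often: 69% at 20% v 40% and 83% at 25% v 50%.

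All of this stands and limits the point. It does not remove the mismatch between a hypothesis of no increased risk and the only comparison the article specifies for categorical safety outcomes.

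**Conclusion.** The point holds in limited form. The Hypothesis section makes a no-excess-harm claim, and the specified difference tests cannot support it at any sample size. The article states no margin and describes no other analysis for it. At 62 per arm, with assumed rates and the assumed trigger for Fisher's test, a doubling of risk would be missed in about 96% of trials at 3% v 6%, 85% at 5% v 10%, 66% at 10% v 20%, 48% at 15% v 30% and 31% at 20% v 40%. It would thus often be missed unless the event is common. The primary analysis and the sample size are unaffected.

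**What to change.** - **Hypothesis:** reword the safety clause as estimation, for example: the trial will estimate the difference in complication risk between the arms, with its 95% confidence interval.
- **Planned analyses, secondary outcomes:** for each key safety endpoint and time point (such as ischemic stroke or intracranial bleeding, and overall morbidity or mortality, at 30 days, 90 days and 1 year), report both rates and the risk difference with a two-sided 95% interval. Use a method suited to sparse events, such as Newcombe or Miettinen–Nurminen. The tests may stay.
- **Same section:** state that a non-significant test will not be reported as no increased risk.

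The cost is wording and extra columns in the safety tables, with no extra patients, visits or data. Neither a larger trial nor a non-inferiority margin is required. The downside is that the sponsor gives up a safety claim the design cannot support.

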### Primary and secondary outcomes

The primary endpoint will be the complete occlusion rate at 6-month follow-up.

Secondary endpoints will include:

1. Immediate technique success rate.

2. Overall morbidity or mortality (assessment time point: 30 days, 90 days and 1 year post-operation).

3. Ischemic stroke or intracranial bleeding (assessment time point: 30 days, 90 days and 1 year post-operation)

4. The rate of intra-stent stenosis (assessment time point: 6 months post-operation)

5. The rate of intra-stent thrombosis (assessment time point: 6 months post-operation)

6. General adverse events (assessment time point: 30 days, 90 days and 1 year post-operation).

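### The printed null and alternative for the primary endpoint are reversed, and contradict the trial's hypothesis, its sample size and its own decision rule

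*Protocol article*

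**What the plan says.** All references are to the protocol article.

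- **Hypothesis:** the flow diverter "may lead to a higher complete occlusion rate and a decreased recanalization rate" compared with stent-assisted coiling.
- **Primary and secondary outcomes:** "The primary endpoint will be the complete occlusion rate at 6-month follow-up". A higher value is better.
- **Sample size:** 65% complete occlusion is assumed with the flow diverter and 35% with stent-assisted coiling, at two-sided α = 0.05 and power 0.80. This gives 49 per arm, raised to 62 per arm for up to 20% withdrawals.
- **Planned analyses, type of test:** "Use superiority test for analysis of primary outcome", and "The superiority margin δ is 0".
- **Planned analyses, symbols:** "Let πT be the rate of complete occlusion rate of treatment group at 6-month follow-up". Correspondingly, πC denotes the same quantity among controls.
- **Planned analyses, test problem:** H0: πT − πC ≥ 0 and H1: πT − πC < 0, with α = 0.05 two-sided.
- **Planned analyses, decision rule:** "The alternative hypothesis will not be accepted unless the lower limit of the 95% confidence interval of the difference of occlusion rate lies above"; what it must exceed is the margin of 0.

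**The concern.** The claim a superiority trial wants to establish belongs in the alternative. Here it sits in the null, and the alternative states that the flow diverter has the lower occlusion rate. The decision rule directly below points the other way. A reader has to choose which of the two to apply, and each choice goes wrong if the rest of the text is taken at its word:

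- **Test the printed pair.** When the device works as planned, the null is almost never rejected. When the device brings no benefit, the null is usually retained as well, and retention could be presented as support for πT ≥ πC although nothing was shown.
- **Follow the interval rule.** A favourable result is then the occasion for accepting a statement that the device is worse.

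This is the only formal statement of the confirmatory test in the document. If it is left as printed, the direction of the primary test has to be inferred by overriding text, possibly after the results are known.

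**Working it through.** **1. Inputs.** Control rate 0.35, flow diverter rate 0.65, two-sided α = 0.05, power 0.80, 1:1 allocation and 20% withdrawals (Sample size). Margin 0, 95% interval for πT − πC, and the printed H0 and H1 (Planned analyses).

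**2. The plan's sample size.** The mean rate is 0.50 and the difference 0.30.

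- Without continuity correction: n = [1.960·√(2·0.50·0.50) + 0.842·√(0.65·0.35 + 0.35·0.65)]² / 0.30² = 42.4, so 43 per arm.
- With continuity correction: n′ = (n/4)·[1 + √(1 + 4/(n·0.30))]² = (42.4/4)·[1 + √(1 + 4/12.72)]² = 48.8, so 49 per arm.
- Withdrawals: 49/0.80 = 61.25, so 62 per arm and 124 in total.

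The printed 49, 62 and 124 are reproduced. The assumed difference is +0.30 in favour of the flow diverter, which lies inside the printed null.

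**3. Direction of each element.**

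| Element | Section | Direction to be shown |
|---|---|---|
| Trial hypothesis | Hypothesis | πT > πC |
| Planning rates 65% and 35% | Sample size | πT > πC |
| Superiority label, margin 0 | Planned analyses | πT > πC |
| Decision rule: lower 95% limit above 0 | Planned analyses | πT > πC |
| Printed H1: πT − πC < 0 | Planned analyses | πT < πC |

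Four elements agree, and the printed pair stands alone. Relabelling cannot rescue it, because πT and πC are defined immediately above it.

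**4. One worked result near the planned effect.** Take 32/49 and 17/49.

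- Difference: 0.653 − 0.347 = 0.306.
- Standard error: √(0.653·0.347/49 + 0.347·0.653/49) = 0.096.
- Wald 95% interval: 0.306 ± 1.96·0.096, that is, 0.118 to 0.495.

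The lower limit is above 0, so the rule's condition for accepting H1 is met. The printed H1 says πT < πC, which these data contradict.

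**5. How often each outcome occurs.** All pairs of binomial counts were enumerated exactly, with Wald 95% limits.

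| Per arm | True rates (T, C) | P(lower limit > 0) | P(upper limit < 0) |
|---|---|---|---|
| 62 | 0.65, 0.35 | 0.935 | 5.1 × 10⁻⁸ |
| 49 | 0.65, 0.35 | 0.864 | 3.2 × 10⁻⁷ |
| 62 | 0.50, 0.50 | 0.029 | 0.029 |
| 49 | 0.50, 0.50 | 0.027 | 0.027 |

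Rejecting the printed null requires the upper limit to fall below 0. With equal rates of 0.50 and 62 per arm, the printed null is retained with probability 1 − 0.029 = 0.971. At common rates of 0.35 or 0.65 the figure is 0.974. The nominal value is 0.975.

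**6. After the signs are exchanged.** With H0: πT − πC ≤ 0 and H1: πT − πC > 0, the same interval rule is the correct criterion. The probability of meeting it at the planning rates is still 0.864 with 49 per arm and 0.935 with 62, and the sample size stays at 124.

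**The case against.** The strongest reply is that only two lines are reversed. The superiority label, the margin, the interval rule and the planning rates all point towards the device being better. An analyst who follows the interval rule tests the intended claim, and under that rule a null result has a lower limit at or below 0 and supports nothing. No competent analyst would report a lower limit above 0 as inferiority. This stands: the likely practical effect is an incoherent formal statement, not a wrong trial conclusion, and swapped signs are the likely cause.

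Two narrower objections also have some force. The rule is worded as a necessary condition for accepting the alternative, so calling it the acceptance criterion is a reading; it is, however, the only criterion given. And 0.935 is simply the power with all 62 per arm contributing. The plan reaches 62 only by allowing for withdrawals, and it lets the per-protocol result decide when the analyses differ, so 0.864 at 49 per arm is the companion figure. These probabilities show how the printed statements behave; they do not measure damage to the trial.

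None of this removes the contradiction. No other text in the article corrects the two lines. Nor is this a detail left to an unseen analysis plan, because the article prints the hypotheses and prints them wrongly.

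**Conclusion.** The concern holds. The null and alternative in Planned analyses are reversed relative to the trial hypothesis, the sample size assumptions, the superiority label and the decision rule in the same section. The printed hypotheses and the printed rule cannot be applied together.

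At 65% against 35%, the data meet the rule's condition with probability 0.935 (62 per arm) or 0.864 (49 per arm), each time contradicting the alternative that would be accepted. A result that rejects the printed null has probability below one in a million at either size. If the rates are equal, the printed null is retained about 97% of the time. These figures rest on the plan's own rates and on Wald intervals, since the article does not name an interval method. The contradiction itself needs no calculation.

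The intended direction is clear, and the sample size is unaffected. It must still be corrected, because this is the formal definition of the confirmatory test and the two statements now give opposite answers.

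**What to change.** In Planned analyses, under the primary outcome, replace the test problem with H0: πT − πC ≤ 0 and H1: πT − πC > 0. Keep the decision rule: superiority is concluded only if the lower limit of the two-sided 95% confidence interval for πT − πC is above 0, which corresponds to a one-sided level of 0.025.

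If a two-sided statement is preferred, print H0: πT = πC and H1: πT ≠ πC, with superiority declared under the same lower-limit condition. Any separate statistical analysis plan should carry the same wording.

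The cost is two lines of text. Data collection, conduct and the 124-patient sample size do not change. The article describes the trial as still recruiting, so on that status the correction can be made and dated before the primary analysis.
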